### Vastus Lateralis Muscle Biopsy Visit

The biopsy will be performed in a similar fashion to previous studies by our group on a separate day with at least 48 hours recovery between other testing visits [64,65]. In brief, the participant will be placed in a supine position. Following an injection of local anesthetic into the skin and fascia (1% Xylocaine), a small incision will be made at the level of the left vastus lateralis. A muscle sample will be taken (~150-300 mg wet weight) using a Bergström biopsy needle with manual suction applied [66]. Once obtained, muscle samples will be processed; cleaned of excess blood, fat, and connective tissue; and split into 3 portions. One portion (10-20 mg) will be immediately immersed in a 5-ml tube containing ~3 ml of biopsy-preserving solution kept on ice and used for in situ measurements of mitochondrial respiration. The second portion (around 20 mg) will be imbedded with Tissue-Tek for the immunohistochemistry analysis. The samples will be immediately frozen in liquid nitrogen and stored at −80°C for subsequent analyses.

### Ethical Considerations

This study has been approved by the Melbourne Health [HREC/15/MH/166] and Victoria University Ethics Committees. The trial has been registered in the Australian New Zealand Clinical Trials Registry [ACTRN12615000906550].

### Outcome Measurements

The primary outcome measure will be exercise tolerance [VO_2peak_ and TTE] during the 2-step CPX test. Secondary outcomes will include measures at rest and during exercise for cardiac function (CO, SV, MAP), as well as peripheral tissue function (lower limb blood flow, endothelial function, PWA, PWV, mitochondrial function). In addition, measures of plasma nitrate and nitrite will be recorded for nitrate-nitrite conversion rate calculations.

### Complications and Adverse Events

Although complications and adverse events associated with the intervention are unlikely, participants will be asked to self-report any symptoms or adverse events they experience. The only previously documented side effects are beeturia (red urine) and red stools [23,67]. Any adverse events noted by the researchers or participants will be reported in the final manuscript.

### Statistical Analysis

The primary endpoint of this pilot study is exercise capacity (VO_2peak_ and TTE) during the maximal CPX in both the HFpEF and HFrEF cohorts. A repeated-measures *t* test will be conducted to determine the changes in exercise capacity variables in the 2 groups combined. This will be followed by a repeated measure analysis of variance to determine the time×group effect in HFpEF and HFrEF patients. Similar analyses will be performed on the secondary endpoints/variables listed in the Specific Aims. Post hoc comparisons of change scores for relevant variables between HFpEF and HFrEF will be performed. Additional pairwise tests as well as linear regressions between the placebo and beetroot juice conditions will be used to determine what physiological factors (mitochondrial efficiency, endothelial function, tissue perfusion, leg blood flow, CO) contribute to any potential changes in exercise tolerance in HFpEF versus HFrEF.

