In comparison with the positive results seen in HFpEF cohorts, data for HFrEF remains limited. A recent study by Hirai et al supplemented HFrEF patients with 12.9 mmol nitrate/day in the form of beetroot juice for 9 days and reported no changes in any of the parameters examined, including exercise performance, central hemodynamics, and blood pressure [31]. The authors suggest that the negative findings could be because HFrEF patients have relatively normal oxygen extraction rates within the peripheral tissues. Although Hirai et al is the only human study examining the effects of inorganic nitrate supplementation on exercise capacity in patients with HFrEF, Coggan et al conducted a study examining the effects of nitrate supplementation on isokinetic knee extensor power [30]. This study showed a 13% increase in the maximal power output following a single dose of inorganic nitrate (11.2 mmol). The authors suggested that the substantial improvement (they note that it is much larger than the 6% increase observed in healthy controls) was due to NO’s known effect of increasing the activation of cyclic guanosine monophosphate. As this activation is known to lead to increases in maximal power output, particularly in type II fibers, it lends further support to nitrate’s efficacy in CHF (where patients are known to be more type II-fiber dominant). In further support of these findings, 2 separate CHF rat model studies, 1 using an acute dose (5 mg/kg sodium nitrite) and 1 using a chronic dose (1 mmol nitrate/kg/day for 5 days), demonstrated significant increases in blood flow and vascular conductance in skeletal muscle [38,39]. The acute sodium nitrite infusion also showed a preferential increase in blood flow, specifically in the muscles of the rats with a higher percentage of both type IIb + IId/x fast-twitch fibers [38]. This further illustrates the potential efficacy of nitrate supplementation within the HFrEF population. Thus, despite the lack of positive findings in the study by Hirai et al, there remains a lot of promise in the use of nitrate supplementation in patients with HFrEF.

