### Objective

The primary aim of this study is to test the hypothesis that 5 days of inorganic nitrate supplementation (16 mmol/day) will improve exercise tolerance (VO_2peak_ and TTE) in both HFpEF and HFrEF patients. We further hypothesize that patients with HFpEF will have larger improvements in exercise tolerance than patients with HFrEF because of greater impairments in their peripheral muscular tissues. The secondary aim of the project is to identify the mechanistic contributors to exercise tolerance in both heart failure classifications via examining the following outcome measures:

Gastrocnemius tissue oxygenation at rest and during submaximal and maximal exercise via near-infrared spectroscopy (NIRS)Vastus lateralis muscle tissue composition and function (angiogenesis, capillaries per unit area and per muscle fiber, mitochondrial function, and muscle fiber composition)Vascular function via brachial artery flow-mediated dilation, lower-limb blood flow via plethysmography, and pulse wave velocity (PWV) and reflection.

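### The hypothesis claims benefit in both HFpEF and HFrEF, but no stated test addresses each cohort: the first test pools them and the follow-ups ask only whether they differ

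*Protocol article*

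**What the plan says.** The Objective section sets the primary hypothesis as better VO2peak and TTE "in both HFpEF and HFrEF patients". It adds an ordering: "We further hypothesize that patients with HFpEF will have larger improvements in exercise tolerance than patients with HFrEF". The Statistical Analysis section defines the primary endpoint as exercise capacity "during the maximal CPX in both the HFpEF and HFrEF cohorts".

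The same section then lists the analyses in this order:

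- A repeated-measures t test that "will be conducted to determine the changes in exercise capacity variables in the 2 groups combined".
- A cohort interaction: "This will be followed by a repeated measure analysis of variance to determine the time×group effect in HFpEF and HFrEF patients".
- "Post hoc comparisons of change scores for relevant variables between HFpEF and HFrEF will be performed".
- Additional pairwise tests and linear regressions between the placebo and beetroot conditions, which "will be used to determine what physiological factors" contribute to any change in exercise tolerance in HFpEF versus HFrEF.

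The Background section reports positive HFpEF studies, one with a 24% gain in TTE. The one human study of exercise capacity in HFrEF "reported no changes in any of the parameters examined, including exercise performance, central hemodynamics, and blood pressure". The same section still sees promise in HFrEF, citing knee-extensor power and rat data. The planned sample is 15 HFpEF and 15 HFrEF patients, each treated under both conditions.

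**The concern.** A hypothesis about both cohorts is two statements, one per cohort. A t test on the 30 patients combined tests a single statement, that the average of the two cohort effects is not zero. One cohort can satisfy that alone. The time×group term and the change-score comparisons test a third statement, that the two effects differ. None of these tests whether HFrEF patients benefit.

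At stake is what the trial may conclude. Its stated contribution is to separate the two classes of heart failure within one protocol. If HFpEF carries the pooled result and the interaction misses the difference, a natural write-up would be that nitrate helps CHF with no evidence of a differential response. That would attribute to HFrEF a benefit that no analysis had shown.

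**Working it through.** **What each stated analysis tests.** Let δP and δR be the mean nitrate-minus-placebo differences in HFpEF and HFrEF.

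| Statement | Quantity |
|---|---|
| Primary hypothesis | δP > 0 and δR > 0 |
| Pooled t test (15:15) | (δP + δR)/2 |
| Time×group ANOVA, change-score comparison | δP − δR |
| Pairwise tests and regressions | physiological contributors |

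With δR = 0 the pooled quantity is δP/2, which is not zero whenever δP is not. This holds at any effect size.

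**Inputs for the size.** The article gives 15 + 15 = 30, justified by feasibility and precedent. It states no alpha, power, effect size, SD or dropout, so there is no power figure to reproduce. Assumed here: two-sided 5%, equal SDs of within-person differences in the two cohorts, no dropout, normal differences, and effects expressed as d = mean difference / SD of differences. Joint probabilities come from 200,000 simulated trials per scenario.

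**Pooled test when only HFpEF responds.** The expected variance of the 30 differences is s² = 1 + (30/29)(d/2)², because the gap between the cohort means adds spread. The critical t on 29 df is 2.045. Approximately, P(positive) = Φ(√30 × d/2 − 2.045 × s):

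- d = 0.8: s = 1.080; 2.191 − 2.208 = −0.02, so about 49%.
- d = 1.0: s = 1.122; 2.739 − 2.294 = 0.44, so about 67%.
- d = 1.2: s = 1.172; 3.286 − 2.396 = 0.89, so about 81%.

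Simulation agrees (first results column).

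**Does the interaction catch it?** With two conditions, the time×group F equals the square of a two-sample t on the change scores: 28 df, noncentrality d × √(15/2).

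| HFpEF d (HFrEF 0) | Pooled positive | Interaction power | Pooled positive and interaction not significant | Interaction not significant, given pooled positive |
|---|---|---|---|---|
| 0.5 | 24% | 26% | 18% | 75% |
| 0.8 | 50% | 56% | 23% | 46% |
| 1.0 | 67% | 75% | 18% | 26% |
| 1.2 | 81% | 89% | 10% | 12% |

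The interaction reaches 80% power only at a between-cohort difference of 1.06 SD.

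**Does pooling lose power?** At HFpEF d = 0.8, an HFpEF-only paired test (n = 15) has 82% power. The pooled test has 50% at HFrEF d = 0, 81% at 0.3 and 88% at 0.4.

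**Requiring each cohort's test to be positive.** If HFrEF has no effect, the false claim of benefit in both is held to about 2.5% at most, whatever the HFpEF effect. The cohorts are independent, so joint power is the square of the one-cohort power:

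| d in each cohort | One cohort (n = 15) | Both (squared) | Pooled (n = 30) |
|---|---|---|---|
| 0.50 | 43.8% | 19% | 75% |
| 0.78 | 80.2% | 64% | 98.5% |
| 0.89 | 89.3% | 80% | 99.7% |

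**The case against.** The strongest reply is that the plan does not stop at the pooled test. It examines heterogeneity, calls itself a pilot, acknowledges its small sample, never labels the pooled t test primary, and states no rule that a positive pooled result establishes benefit in both cohorts. A condensed article may also leave the exact form of the additional pairwise tests to a fuller document.

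Much of this stands, and it rules out three stronger readings:

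- A reader might infer that every positive pooled result would be taken as support for both cohorts. The documents do not say so. The planned interaction would often flag the difference, which is why the relevant figures are 23%, 18% and 10% rather than 50%, 67% and 81%.
- A reader might infer that pooling generally wastes power. The protocol predicts improvement in both cohorts with HFpEF larger; it does not predict a zero HFrEF effect. With HFrEF at 0.3 to 0.4 SD, pooling costs essentially nothing or gains power.
- A reader might infer that the pooled test should be dropped. With 30 patients that is a debatable trade, since cohort-specific claims need much larger effects.

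What the reply does not remove is the mismatch. The pooled test is the first one named, directly after an endpoint defined in both cohorts. The pairwise tests are given a mechanistic purpose. A non-significant interaction at 15 versus 15 is not evidence that HFrEF benefits.

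**Conclusion.** The point holds as a mismatch between hypothesis and test, and it should be fixed. That no stated analysis tests benefit in each cohort follows from the text and needs no assumed effect size.

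How often it would mislead does rest on assumptions: those listed in the working, and above all an HFrEF effect at or near zero. That is plausible given the one null HFrEF exercise study, but not certain. On that basis roughly one trial in four to one in ten, for HFpEF effects of 0.8 to 1.2 SD, would end with a positive pooled test and no significant interaction. The loss of power from pooling is confined to an HFrEF effect near zero. Pilot status lowers the stakes but does not make the pooled test answer the stated question.

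**What to change.** In the Statistical Analysis section, or in the analysis plan before unblinding:

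1. Keep the pooled test as the test of an effect in CHF overall, and word its conclusion that way.
2. Add the nitrate–placebo difference in VO2peak and in TTE within each cohort, with 95% CIs, from one mixed model with treatment, period, cohort and treatment×cohort.
3. Claim benefit in both cohorts for a given endpoint only if each cohort's own test is significant at 5%. No alpha adjustment across cohorts is needed, because both must succeed. State that a non-significant interaction is not support for the claim.
4. State for each of VO2peak and TTE which claim it supports. The both-cohorts rule does not settle multiplicity across the two measures.

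This needs no extra patients or visits, and data collection was still under way when the article was written. The price is that the both-cohorts claim becomes harder to reach: 80% joint power needs about 0.89 SD in each cohort, whereas the pooled test has 80% power at about 0.53 SD. If that is too demanding for a pilot, rewording the primary hypothesis to CHF overall, with cohort estimates as secondary, also resolves the mismatch.

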## Results

Data collection from this paper is currently underway. Predicted completion of the recruitment phase is mid-2018.

## Discussion

### Principal Findings

Heart failure is a chronic, progressive condition that has deleterious effects on both the central and peripheral function of the body, resulting in the hallmark symptom of exercise intolerance. This decrease in aerobic capacity is linked with lower rates of survival, a higher burden of disability, and increased rates of hospitalization for patients with CHF and is a prime target for rehabilitative interventions [4,68]. Thus, interventions that can acutely improve the tolerability of exercise for these patients could represent a crucial step forward for treatment.

The proposed project will be the first to comprehensively compare the central and peripheral function at rest and during exercise in both HFpEF and HFrEF patients on and off nitrate supplementation. This study will also be the first study in CHF that assesses the effects of nitrate supplementation within the skeletal muscle tissue (mitochondrial function, capillary density, and muscle fiber composition). Results from previous trials (in healthy individuals) have indicated the potential beneficial impact of nitrate supplementation on mitochondrial function, but this mechanistic change has yet to be demonstrated in CHF patients [21].

### Limitations

The sample size for this study, although larger than some comparable trials, is still quite small. However, the crossover design helps to reduce the potential variability and improve the possibility of detecting differences between both the placebo and beetroot juice groups and the HFpEF and HFrEF groups. The high chronic dose was chosen to maximize the potential benefits of the supplementation, but the authors note that the amount is much higher than what would be consumed naturally in the diet. Finally, although every effort will be made to keep the supplementation days consistent before each testing visit between the placebo and beetroot juice rounds, because of patient and medical team availability, it is not possible to fully control this aspect. The 5-day loading period before any testing should help to standardize the dosing days. However, we will report any difference in dosing days between the 2 treatment arms.

### Conclusions

Our understanding of the potential effects of nitrate supplementation in patients with CHF is still in its infancy. Although the initial studies show promise, the studies have been small and limited in scope to just 1 classification of CHF. This is the first study to directly compare the effects of inorganic nitrate supplementation on patients with HFrEF and HFpEF following an identical protocol to tease out any changes (and/or differences in changes) in peripheral and central factors. This is a critical step in advancing our current knowledge of CHF as a disease as well as the efficacy of nitrate supplementation. Given the relationship between exercise capacity and mortality and morbidity, if inorganic nitrate supplementation can improve exercise tolerance in patients with CHF, it has the potential to aid in further refining the treatment of patients in this population.

## Abbreviations

CHF: chronic heart failure
CO: cardiac output
CPX: cardiopulmonary exercise test
FMD: flow-mediated dilation
HFpEF: heart failure preserved ejection fraction
HFrEF: heart failure reduced ejection fraction
MAP: mean arterial pressure
MLHFQ: Minnesota Living With Heart Failure Questionnaire
NIRS: near-infrared spectroscopy
NO: nitric oxide
PAQ: Physical Activity Questionnaire
PWA: pulse wave analysis
PWV: pulse wave velocity
SEES: Subjective Exercise Experience Scale
SNS: sympathetic nervous system
SV: stroke volume
TTE: time to exhaustion
VO2peak: peak oxygen consumption
